### Eligibility criteria

#### Inclusion criteria

All of

Paracetamol overdose presenting to hospital within 24 hours of taking their last dose of paracetamol. All patterns of overdose (single, staggered overdoses and therapeutic excess); accidental or deliberate; paracetamol alone or mixtures of tablets are eligible.Patient deemed to need NAC treatment by the clinical team.Blood paracetamol concentration and alanine aminotransferase (ALT) results are available (clinical care bloods).Provision of informed consent.Adult (16 years old or above).

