### Recruitment

#### Identification

Patient screening will be undertaken by the nurses of the Emergency Medicine Research Group of Edinburgh. Participant eligibility will be verified by a delegated clinical trial physician after written informed consent has been obtained. Confirmation of eligibility will be recorded within the participants’ medical records and the participant added to the screening log.

The need for NAC treatment will be determined by the blood paracetamol concentration and liver function tests (including ALT) which are measured as part of routine care. Results from routine blood samples taken between 4 hours and 24 hours after the last ingestion of paracetamol overdose may be used for this eligibility assessment.

Pregnancy testing will be carried out prior to randomisation if a potential participant is of childbearing potential and could be pregnant, and this will be recorded in the patient’s medical notes and the electronic case report form (eCRF). Childbearing potential is defined as fertile, following menarche and until becoming postmenopausal unless permanently sterile. Permanent sterilisation methods include hysterectomy, bilateral salpingectomy and bilateral oophorectomy. A postmenopausal state is defined as no menses without an alternative medical cause for 12 months for women over 50 years old and for 24 months for women under 50 years old. A high follicle-stimulating hormone (FSH) level in the postmenopausal range may be used to confirm a postmenopausal state in women not using hormonal contraception or hormonal replacement therapy. However, in the absence of 12 months of amenorrhoea, a single FSH measurement is insufficient.

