#### Randomisation

Randomisation will be carried out using a web-based randomisation service (managed by the Edinburgh Clinical Trials Unit (ECTU)). Participants will be randomised by any appropriately delegated member of the trial team to Standard NAC (300 mg/kg), HiSNAP Group 1 (450 mg/kg) or HiSNAP Group 2 (600 mg/kg) in a 1:1:1 ratio and minimised according to whether a patient meets the criteria of being at high risk of liver injury after overdose. High risk is defined as a hospital presentation ALT activity greater than the upper limit of normal (defined as >50 U/L) or a blood paracetamol concentration over the 300 line on the nomogram (applies only to single-acute overdoses; figure 4). A random element will be included in the minimisation to maintain unpredictability.

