**Figure 4 F4:**
[figure not shown]
Nomogram used in UK clinical practice to determine if treatment is required for paracetamol overdose (100 line) and line used for trial purposes to determine if single-acute overdoses are over the 300 line.

Once a patient is randomised, they will remain in the study and have all outcomes recorded regardless of compliance with study allocation, unless they specifically withdraw consent to have data stored.

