### Sample size and analysis plan

We have profiled paracetamol metabolites using samples from the SNAP and MAPP trials (%GSH mean 2.16% (SD 1.81)).^17^ External validity is provided by a recent Australian cohort study that reported similar mean and SD for these metabolites.^21^ To detect a 45% difference in this toxicokinetic marker between standard and each of the HiSNAP groups (cf 50% effect size estimated from mouse pilot data), 30 patients per group will give a power of 88% (log-transformation of data, 5% two-sided significance level, analysis by analysis of covariance adjusting for baseline value, assuming correlation 0.62 between baseline and post-NAC %GSH). To control the overall type I error at 5%, we will incorporate a hierarchical hypothesis testing structure. We will first test the primary outcome on the HiSNAP Group 2 against Standard NAC; only if that is significant will we test HiSNAP Group 1 against Standard NAC. Patients with liver injury (and by definition, excessive NAPQI production) have an increase in metabolites of between double to fourfold (200–400%). Therefore, our study is powered to detect a clinically relevant effect size (45%).

The log-transformed primary outcome, %GSH metabolites, will be analysed using a normal linear model, adjusting for the pre-NAC %GSH value and for the continuous form of the baseline variables ALT and blood paracetamol concentration on which the minimisation factor is based. The treatment effect for each HiSNAP group versus Standard NAC will be estimated using the least-squares mean difference and its 95% CI, back-transformed to the original scale to give the ratio for HiSNAP:Standard NAC.

Continuous secondary outcomes will be analysed in the same way as the primary outcome. Categorical secondary outcomes will be analysed using logistic regression, adjusting for the minimisation variables in the same way as in the normal linear model and reporting the treatment effect in each HiSNAP group versus Standard NAC by OR (95% CI). A detailed statistical analysis plan will be finalised prior to database lock and unblinding of the trial statistician.

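### The primary model leaves out the high-risk flag used for minimisation, and ALT plus paracetamol concentration do not reproduce it

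*Protocol article*

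**What the plan says.** The Randomisation section of the protocol article uses a single balancing factor: participants are "minimised according to whether a patient meets the criteria of being at high risk of liver injury after overdose". The flag has two limbs joined by an or. The first is biochemical: "High risk is defined as a hospital presentation ALT activity greater than the upper limit of normal (defined as >50 U/L". The second is a "blood paracetamol concentration over the 300 line on the nomogram (applies only to single-acute overdoses". The caption to Figure 4 repeats that the line serves to classify single-acute overdoses.

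The section on sample size and analysis lists the covariates of the primary model: the pre-NAC %GSH value, and a further adjustment "for the continuous form of the baseline variables ALT and blood paracetamol concentration on which the minimisation factor is based". The flag itself is not listed, nor is time since ingestion or overdose pattern. Continuous secondary outcomes are to be handled as the primary is, and the logistic models for categorical outcomes carry over the same adjustment.

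Two other sections matter. The inclusion criteria admit "All patterns of overdose (single, staggered overdoses and therapeutic excess"). The Identification section allows "Results from routine blood samples taken between 4 hours and 24 hours after the last ingestion" to be used for the eligibility assessment.

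**The concern.** Replacing a dichotomy by the continuous variable behind it is usually good practice, because it keeps information and still accounts for the balancing. That argument needs the continuous variable to be the one that was cut. ALT meets this condition; paracetamol concentration does not, because the second limb compares concentration with a line on a nomogram, and only in one type of overdose.

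When a prognostic variable has been used to balance the arms but is missing from the model, its between-patient variation stays in the residual although the design has removed it from the treatment contrast. Model-based standard errors are then too large and the test is conservative. There is reason to expect the flag to be prognostic. The protocol article says that metabolites are two to four times higher in patients with liver injury, and that patients over the 300 line are at high risk of liver injury even with NAC. With 30 patients per arm and a hierarchical test, power lost in the 600 mg/kg comparison also bears on whether the 450 mg/kg comparison is tested at all.

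**Working it through.** **1. The plan's own figure.** The plan states 88% power with 30 per group. Inputs: mean 2.16, SD 1.81, correlation 0.62, a 45% difference, two-sided 5%. No log-scale SD is given, so I assume a log-normal distribution.

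- SD of log = √ln(1 + (1.81/2.16)²) = 0.729
- SD after baseline adjustment = 0.729 × √(1 − 0.62²) = 0.572
- Power = Φ(ln 1.45 / (0.572 × √(2/30)) − 1.96) = Φ(0.372/0.148 − 1.96) ≈ 71% (70% with the t distribution)

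This does not reproduce 88%, which would need an unadjusted log SD of 0.585. That is a separate matter. It is shown only to explain why the powers in step 3 start near 69%; what counts there is the difference between models.

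**2. Can the listed covariates reproduce the flag?** Write C for concentration, t for time since ingestion and L(t) for the 300 line.

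- Flag = 1 if ALT > 50, or if the overdose is single-acute and C > L(t).
- Model covariates: pre-NAC %GSH, ALT, C.

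*Pattern.* Take two patients with the same normal ALT and the same C, above the line. One took a single-acute overdose, so the flag is 1; the other took a staggered overdose, so the flag is 0. Their ALT and C terms are identical. This needs no assumption about the line.

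*Time.* Figure 4 is not shown, so the line is assumed to be 300 mg/L at 4 h and to halve every 4 h. It is then 150 at 8 h and 75 at 12 h, so C = 150 is half the line at 4 h, on it at 8 h and twice it at 12 h. With halving every 3 to 5 h, the line at 8 h is 119 to 172. C = 200 is then below the line at 4 h and above it at 8 h throughout that range. I take the 4–24 h eligibility samples to be those that feed the flag.

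**3. What does omitting the flag cost?** Simulation of 4,000 trials per scenario: 90 patients, minimisation with a 0.8 random element, residual log SD 0.572, log baseline %GSH unrelated to the flag, and untransformed ALT and concentration. The assumed patient mix has about 29% flagged. In it, ALT and concentration together explain about 41% of the flag's variance. The flag effect is the part on log %GSH not carried by baseline %GSH.

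| Flag effect (log units) | Power at 1.45, plan's covariates | Power with flag added | Type I error, plan's covariates | Type I error with flag added |
|---|---|---|---|---|
| 0 | 68.6% | 68.6% | 4.7% | 4.7% |
| 0.35 | 66.8% | 68.4% | 5.1% | 5.2% |
| 0.70 | 62.7% | 69.4% | 4.4% | 5.2% |

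The Monte Carlo standard error of one power figure is about √(0.67 × 0.33/4000) = 0.7 points, and of one type I error about √(0.05 × 0.95/4000) = 0.3 points. Both models were fitted to the same simulated data, so differences are more precise than that. At an effect of 0.70 and a ratio of 1.45, the plan's model SE averages 0.162 against a true SD of 0.152 (0.162/0.152 = 1.06); with the flag the model SE is 0.150. Mean treatment estimates were 0.371 to 0.372 in these two scenarios, with or without the flag, against a true 0.372.

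**4. How large might the residual effect be?** An effect of 0.70 is close to ln 2 = 0.69, a doubling not carried by baseline %GSH at all. If a doubling is already present in the pre-NAC sample, baseline %GSH absorbs part of it and 0.69 × (1 − 0.62) = 0.26 remains; for a fourfold rise, 1.39 × 0.38 = 0.53. A second simulation (3,000 trials, 19% flagged) gave 67.8% to 68.4% and 66.0% to 69.3% for these two cases. With the whole rise appearing only after NAC, it gave 65% to 70% for doubling and 53% to 69% for fourfold.

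**The case against.** The best defence is that adjusting for continuous ALT and concentration is openly prespecified, defensible and causes no bias. Any error is in the conservative direction, and baseline %GSH will probably carry much of the flag's prognostic value. All of this stands, and it is why the point is a modest one. It does not restore the claim that concentration is what the factor is based on: the single-acute restriction alone breaks that link.

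A reader might go further and infer that ALT, concentration and pre-NAC %GSH enter untransformed, so that skewness costs additional power. The text does not say so. It contrasts continuous with dichotomised, names no covariate scale, and mentions log-transformation in the power statement. Covariate scale is ordinary analysis-plan detail. Nor is logging a clear gain for the flag: in the simulated mix, log ALT and log concentration explained less of it (33%) than the untransformed forms (41%). Comparing logged covariates plus the flag with unlogged covariates alone would show a wider power gap, but it mixes two changes and cannot be charged to the missing flag.

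A reader might also take the two- to fourfold rise as the effect of the flag. The protocol article attaches it to patients with liver injury, not to everyone over a presentation threshold, and does not say that it is absent before NAC. The largest gain in step 4 therefore has no support as the expected case.

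**Conclusion.** The mismatch is real and can be read from the text: the model omits the only balancing factor, and the covariates that replace it cannot reconstruct it without overdose pattern and sampling time. The documents do not support a claim of bias or of inflated type I error. The consequence is a possible loss of efficiency, from nothing if the flag is inert to about 7 power points (69.4 − 62.7 = 6.7) if it carries a residual effect equal to a doubling. The size rests on an assumed patient mix, line shape, sampling times and log-normal SD; the existence of the mismatch rests on none of these. Severity: consider.

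**What to change.** Add the binary high-risk factor, with the value used in the minimisation, to the primary model and to the linear and logistic secondary models that copy it. Keep pre-NAC %GSH, ALT and paracetamol concentration as they are. One sentence in the analysis plan suffices, and that plan is still to be finalised before database lock.

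The cost is one degree of freedom per model. With all 90 patients, the primary model goes from 90 − 6 = 84 to 83 residual degrees of freedom. No new data are needed, because the flag is already determined for every randomised patient. If the flag turns out to be inert, the simulated power is unchanged.

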### Safety assessments

Participants will be asked about the occurrence of AEs/SAEs at every visit during the study. Open-ended and non-leading verbal questioning of the participant will be used to enquire about AE/SAE occurrence. Participants will also be asked if they have been admitted to hospital, had any accidents, used any new medicines or changed concomitant medication regimens. If there is any doubt as to whether a clinical observation is an AE, the event will be recorded. AEs and SAEs may also be identified via information from support departments, for example, laboratories or participant questionnaires.

The symptoms questionnaire will be reviewed as soon as possible after completion and within 7 days if the questionnaire is available and any clinically significant events identified by the principal investigator (PI) (or delegated physician) will be recorded/reported as AEs/SAEs. A clinically significant event is defined as one which requires treatment and/or is recorded in the medical records.

Anaphylactoid reactions and cerebral oedema are AESI and will be recorded and reported. The DMC will review the occurrence of AESI and their related symptoms by treatment group at each meeting. Any cases of confirmed cerebral oedema confirmed by the PI will immediately halt the trial and mandate DMC review before any further participants are randomised as this is a stopping criterion.

### Monitoring and oversight

The HiSNAP trial is an investigator-led study, sponsored by the Academic and Clinical Central Office for Research and Development for NHS Lothian/University of Edinburgh (ACCORD, reference AC23035, [contact]). Trial oversight is directly provided by an independent Trial Steering Committee and a separate independent DMC who will provide advice and review of safety.

### Study amendments and current status

The study protocol currently in effect is V.6, 3 July 2024. A protocol version history is provided in online supplemental 1. Recruitment commenced 20 March 2024. At the time of authorship, 16 patients have been recruited and the trial is expected to complete recruitment on schedule.

## Ethics and dissemination

The trial will be conducted according to the ethical principles of the Declaration of Helsinki 2013 and was approved by the East Midlands (Derby) Research Ethics Committee, 26 September 2023 (reference 23/EM/0129), NHS Lothian Research and Development Department and the MHRA. Good Clinical Practice regulations will be followed, and written informed consent will be obtained from all participants. A copy of the consent form is provided as online supplemental material.

No trial results will be shared while the trial is ongoing. When the trial completes, data will be shared via presentation, publication and may be available on request from the trial chief investigator, decided on a case-by-case basis. Data sharing may be restricted in line with patent or commercial requirements for as short a time as possible.

Results will be disseminated by peer-reviewed publication, conferences and linked on isrctn.com. Publication content will follow the Reporting of surrogate end points in randomised controlled trial reports (CONSORT-Surrogate) Extension of the CONSORT 2010 statement.^22^ Ownership of data arising from this study resides with the study team at the Sponsor Organisation. The study team will follow the International Committee of Medical Journal Editors guidelines on authorship. Requests for data access should be sent to the corresponding author.
